# SlowMo, a digital therapy targeting reasoning in paranoia, versus treatment as usual in the treatment of people who fear harm from others: study protocol for a randomised controlled trial

**DOI:** 10.1186/s13063-017-2242-7

**Published:** 2017-11-02

**Keywords:** Delusions, Persecutory, Fast and slow thinking, Belief flexibility, Jumping to conclusions, mHealth, eHealth, Digital therapy, User-centred design

## Abstract

**Background:**

Paranoia is one of the most common symptoms of schizophrenia-spectrum disorders, and is associated with significant distress and disruption to the person’s life. Developing more effective and accessible psychological interventions for paranoia is a clinical priority. Our research team has approached this challenge in two main ways: firstly, by adopting an *interventionist causal approach* to increase effectiveness and secondly, by incorporating *user-centred inclusive design methods* to enhance accessibility and usability. Our resultant new digital intervention, SlowMo, intensively targets a reasoning style associated with paranoia, *fast thinking,* characterised by jumping to conclusions and belief inflexibility. It consists of an easy-to-use, enjoyable and memorable digital interface. An interactive web-based app facilitates delivery of face-to-face meetings which is then synchronised with an innovative mobile app for use in daily life.

**Methods/Design:**

We aim to test the clinical efficacy of SlowMo over 24 weeks to determine the mechanisms through which it reduces paranoia, and to identify participant characteristics that moderate its effectiveness. In a parallel-group randomised controlled trial, with 1:1 allocation, 360 participants with distressing persecutory beliefs will be independently randomised to receive either the SlowMo intervention added to treatment as usual (TAU) or TAU, using randomly varying permuted blocks, stratified by paranoia severity and site. Research workers will be blind to therapy allocation. The primary outcome is paranoia severity over 24 weeks; our hypothesised mechanism of change is reasoning; moderators include negative symptoms and working memory; and secondary outcomes include wellbeing, quality of life, and service use. The accessibility, usability and acceptability of the digital platform will be assessed.

**Discussion:**

SlowMo has been developed as the first blended digital therapy to target fears of harm from others through an inclusive design approach. In addition to testing its efficacy, this trial will add to our understanding of psychological mechanisms in paranoia. The study will examine the usability and adherence of a novel digital therapy, including an app for self-management, in a large sample of people affected by severe mental health difficulties.

**Trial registration:**

ISRCTN registry, ID: ISRCTN32448671. Registered prospectively on 30 January 2017. Date assigned 2 February 2017.

**Electronic supplementary material:**

The online version of this article (doi:10.1186/s13063-017-2242-7) contains supplementary material, which is available to authorized users.

## Background

People often experience distressing fears about other people intentionally causing them harm: this is known as paranoia [1]. The severity of paranoia lies on a continuum, ranging from fleeting ideas that someone on the street might be laughing at us, to more elaborate and persistent beliefs (sometimes called persecutory delusions) such as that the secret services are trying to have us killed. Paranoia is one of the most common symptoms of schizophrenia-spectrum disorders, and is associated with significant distress and disruption to the person’s life [2]. This results in increased use of services, including inpatient admissions, and high costs to mental health care providers. Developing effective interventions for paranoia is, therefore, a clinical priority. The National Institute for Health and Care Excellence (NICE; 2014) recommends cognitive-behavioural therapy for psychosis (CBTp), including paranoia [3]. However, there are significant challenges to access, engagement, adherence and effectiveness [4–6]. CBTp has relatively high training and delivery costs, which limits availability. Even when it is offered, people may be reluctant to engage in therapy, and can struggle to remember what is discussed or apply new learning to daily life. Recent meta-analytical studies of CBTp have found small- to medium-sized beneficial effects on paranoia, and a pressing need to improve outcomes has been identified [6]. Our research team has approached this challenge in two main ways: firstly by adopting an *interventionist causal approach* [7] to increase CBTp effectiveness and secondly by incorporating *user-centred inclusive design methods* to enhance accessibility and usability. Our resultant new digital intervention, SlowMo, aims to improve the appeal, ease of use, memorability and clinical effectiveness of psychological therapy for people who fear harm from others.

The interventionist causal approach to improving therapy effectiveness involves first identifying mechanisms that play a causal role in paranoia (e.g. reasoning, worry, negative self-beliefs, safety behaviours and sleep dysfunction) and then developing tailored interventions to target these causal processes [8, 9]. These targeted interventions are anticipated to reduce paranoia severity through different pathways given the multifactorial causality of paranoia. For example, a recent randomised controlled trial of a brief intervention focussed on worry processes demonstrated that reductions in this mechanism accounted for improvements in paranoia [10]. In contrast, SlowMo works by intensively targeting a certain type of thinking associated with paranoia, which can be thought of as *fast thinking* [11–13]. Fast thinking is characterised by focussing on too little information (‘jumping to conclusions’) and belief inflexibility (high conviction in thoughts and a lack of consideration of alternative ideas [13]). It has been robustly linked to paranoia [8, 12–17]. Systematic attempts to modify this style of reasoning include group-based, metacognitive training (MCT) and, more recently, individual training (MCT+) developed by Moritz and colleagues [18]. Whilst earlier findings for MCT were promising, more robust designs have not shown consistent improvements in reasoning, or paranoia at long-term follow-up, particularly for those with more severe difficulties [19–21].

The SlowMo intervention builds on the important work of Moritz and colleagues and is the endpoint of a decade of development and testing in four studies targeting fast thinking in paranoia [12, 22–24]. The first versions of the intervention were tested iteratively, in three randomised studies and one case series, with developments over time in intervention content, duration and name, whilst always targeting aspects of fast thinking and paranoia [12, 22–24]. We found reductions in unhelpful fast thinking and improvements in paranoia severity. In an experimental study [12] designed to examine mediation, we found preliminary evidence that changes in belief flexibility mediated improvements in paranoia. Most recently, in a feasibility randomised controlled trial, 31 participants with paranoia were recruited and randomly allocated 2:1 to the Thinking Well intervention or treatment as usual (TAU) [24]. The intervention involved face-to-face sessions with a therapist, initially working on a brief computer-based programme targeting reasoning biases [23] followed by four additional therapy sessions (with no additional digital component) aimed at generalising the learning to real-world situations. We found reductions in fast thinking (belief flexibility and jumping to conclusions) and promisingly large effects (effect size *d* = 1.1) on paranoia severity. However, assessments were not blinded and the sample size was small. Further, whilst the acceptability of the intervention was high, participants suggested ways in which the intervention could be made more personalised, enjoyable and applicable to daily life. Our experimental work also indicated that people with more working memory difficulties and negative symptoms benefitted less from the therapy. This current iteration (SlowMo) shares the focus on reasoning of its predecessors (Maudsley Review Training Programme [23] and Thinking Well [24]). However, whilst previous versions of the intervention relied on verbal presentation of material using PowerPoint and pen-and-paper tools, SlowMo uses a website and app for interactive, multimodal communication of information, together with consistent use of normalising (everyday) language.

Incorporating digital technologies into psychological interventions presents unique opportunities for improving outcomes, understanding mechanisms of change and reducing costs [25–27]. However, to deliver meaningful change in health care, digital solutions need to be tailored to meet the specific needs of their users and to be trustworthy with regard to safety, privacy and effectiveness [28–31]. To meet this challenge, the development of SlowMo therapy has involved a *user-centred inclusive design* approach. Inclusive design aims to address the needs of the broadest range of users possible, a crucial issue given the heterogeneity of psychosis. Our design approach was informed by the Design Council’s double diamond method [32], which comprises the following phases: discover, define, develop and deliver. Importantly, stakeholders (service users, clinicians, researchers, technologists, innovation design engineers), including sampling of ‘extreme’ users [33], were involved from the outset, with iterative exploration, prototype testing and feedback informing the design and development of SlowMo.

SlowMo aims to assist people with paranoia by supporting them to notice their upsetting concerns and fast-thinking habits, and then providing them with strategies to *slow down for a moment* in order to focus on new information and develop safer thoughts [34]. It consists of an easy-to-use, enjoyable and memorable digital interface. Thoughts are visualised as bubbles, with different speeds, sizes and colours reflecting different thinking habits, intensities of emotion and coping tips. This simple visual metaphor aims to help people to understand that thoughts are transient, and that we can modify them by using coping strategies. Based on session content from earlier work, an interactive web-based app facilitates the delivery of face-to-face meetings. This is then synchronised with an innovative, mobile app for use in daily life, which is ‘native’ (i.e. one that runs on the phone and can work offline). Feasibility testing of an early prototype has been conducted with acceptability, usability and enjoyment assessed through a self-report 10-item User Experience Survey, adapted from use in a previous study examining the feasibility of a mobile app for the management of psychosis [35]. The measure generates a mean percentage for each dimension of user experience, ranging from 0 (totally disagree) to 100 (totally agree). Results were extremely positive, with high rates of acceptability, usability and enjoyment (>75%). Participants indicated that they significantly preferred the digital interface to conventional therapy materials. This is particularly encouraging in the context of digital interventions given recent evidence that overall uptake of a therapeutic app for psychosis delivered in a naturalistic setting was low [30]. Given these data on the digital interface, together with the proof-of-concept, feasibility and acceptability evidence from our four preliminary studies [12, 22–24], we are now well placed to test the SlowMo intervention in a fully powered, larger, methodically rigorous, multisite randomised controlled trial.

### Aims

We aim to test the clinical efficacy of SlowMo over 24 weeks compared to TAU to determine the mechanisms through which it reduces paranoia, and to identify participant characteristics that moderate its effectiveness (either by moderating the degree of change in the mechanism, or by influencing adherence to the intervention). We will test the hypothesis that changes in fast thinking mediate changes in our primary outcome of paranoia severity. Consistent with our interventionist causal approach, we do not hypothesise that worry is a mediator, as it is not targeted in the SlowMo intervention, even though changes in worry did mediate changes in paranoia in a recent trial, when it was the treatment target [10]. However, we will examine any observed effects. In addition, we have preliminary evidence of modifiers of treatment effects that we will also take the opportunity to investigate. Using a randomised controlled trial design, we have selected TAU as the comparator condition. This is because there is a very low penetration of evidence-based psychological treatment in the NHS, and thus the key efficacy question to address at this stage is whether SlowMo confers benefits over and above standard care. An important secondary goal is to evaluate mechanisms of action; the trial hypotheses concern reasoning, and are best tested where the control condition is inactive with respect to the targeted psychological processes.

The main research questions are as follows:Is SlowMo efficacious in reducing paranoia severity over 24 weeks, when added to TAU, in comparison to TAU alone?Does SlowMo reduce paranoia severity by improving fast thinking (reducing belief inflexibility and jumping to conclusions)?Do participant characteristics (i.e. their cognitive capacities, specifically working memory and thinking habits; and their symptoms, specifically negative symptoms) moderate the effects of the intervention?Does outcome differ by adherence to the intervention and is adherence predicted by the participants’ beliefs about their illness and about the intervention?Does the SlowMo digital therapy platform have acceptable rates of usability, acceptability and adherence?Does SlowMo lead to changes in the following secondary outcomes: other delusional symptoms, wellbeing, quality of life, self and others schemas, service use and worry

### Hypotheses

Primary hypotheses:The intervention will reduce paranoia severity over 24 weeksFast thinking (belief inflexibility and jumping to conclusions) will improve in response to the interventionReductions in fast thinking will mediate positive change in paranoia severity

Secondary hypotheses:4.Poorer working memory and more severe negative symptoms will negatively moderate treatment effects5.Therapy adherence will moderate the effects of treatment on outcome and adherence will be predicted by beliefs about mental health problems6.Worry will not mediate reductions in paranoia severity

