### Sample size

Recruitment of 360 participants will be split equally across sites. We have powered the study conservatively to detect a clinically meaningful 10-point reduction in the primary outcome measure (GTPS [36]); based on a standard deviation of 25, this is a 0.4 effect size [10]. We account for: clustering in the SlowMo arm with an intraclass correlation coefficient (ICC) = 0.01 with 10 therapists (no clustering in the TAU arm), 1:1 allocation, 0.05 significance level. Calculations used Clsampsi in Stata. A simple two-tailed *t* test with 150 people per group gives 90% power to detect an effect size of 0.4, and 80% for 0.35. In practice, power will be increased by using multiple regression. To allow for conservatively high 20% attrition we will recruit 360 patients at baseline split equally across three sites (120 per site, 60 per arm per site). For the mediational analyses, a sample of *N* = 300 has > 80% power to detect a proportion mediated of 40%, and > 70% power to detect a proportion mediated of 30%, corresponding to findings in our pilot work [12] (calculated using PowerMediation in R).

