### Statistical analysis

We will report all participant flow, and analyses will be conducted on the ITT population: all participants will be randomised regardless of non-compliance with protocol or withdrawal from the study. Analyses will post-date final follow-up assessments, with due consideration of potential biases from loss to follow-up. The primary analysis will test for a treatment effect on the primary and secondary clinical outcomes. Random effects regression models allowing for clustering by both participants and therapists will be fitted to the repeated measures, controlling for treatment site, baseline paranoia severity and the corresponding baseline assessment for the outcome under investigation. We will allow for missing outcome data under the Missing At Random assumption [60]; we may also use inverse probability weighting to adjust for non-adherence to allocated treatment and other intermediate outcomes as predictors of future loss to follow-up [61]. Secondary analyses will test treatment-effect mechanisms, moderation and process/adherence effects using modern causal inference methods [62, 63]. The trial outcomes will comprise two parallel series of longitudinal data: one for the putative mediators (M) and one for the clinical outcomes (Y).

For the mechanistic analysis, to test for a treatment effect on the putative mediator, we will replace the clinical outcome with the mechanistic variable as the dependent variable in the random-effect models. If we separately demonstrate a treatment effect on both the putative mediator and on the clinical outcome, we will evaluate mediation in these parallel longitudinal data sets through the use of parallel growth curve and latent change models [64, 65]. These models preserve the basic mediation model by replacing observed variables with latent constructs – the growth factors driving the temporal responses, M_1_ to M_p_ and Y_1_ to Y_p_. Importantly, the mediational structure only applies to the slope growth or change factors since randomised treatments are independent of the intercept growth factors (baseline values). Growth curve and latent change models can be estimated by maximum likelihood and other methods using the software package Mplus [66]. The application of these methods to mechanism evaluation within EME (Efficacy and Mechanism Evaluation) trials is illustrated in [62]

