The aim of these analyses is to demonstrate that the effect of treatment on the growth (change) in the clinical outcome (Y) is explained (caused) by its effect on the growth (change) in the mediator. The major challenge to a valid inference is that there may be confounding of the mediator and outcome. We will begin by allowing for baseline values of the mediator and of the clinical outcome, as in the analyses of the successful EME Worry Intervention Trial [10]. We will then check the sensitivity of the results to the possibility of hidden confounding (unmeasured variables) through the use of instrumental variable methods [62, 63].

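### Secondary hypothesis 6 predicts that worry will not mediate, but the mediation analysis described can only detect mediation, so a null result would not show it is absent or small

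*Protocol article*

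**What the plan says.** The Hypotheses section gives, as the last of three secondary hypotheses: "Worry will not mediate reductions in paranoia severity".

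The Aims section puts it differently: "we do not hypothesise that worry is a mediator, as it is not targeted in the SlowMo intervention". It notes that worry did mediate change in paranoia in a recent trial that targeted worry, and adds: "However, we will examine any observed effects". It also lists worry among the secondary outcomes that SlowMo may change.

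The Statistical analysis section sets a precondition for the mediation models: "If we separately demonstrate a treatment effect on both the putative mediator and on the clinical outcome, we will evaluate mediation". It then gives their purpose: "The aim of these analyses is to demonstrate that the effect of treatment on the growth (change) in the clinical outcome (Y) is explained" by the effect on change in the mediator.

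The Sample size section gives power only for detecting mediation: at N = 300, above 80% for a proportion mediated of 40% and above 70% for 30%. The article gives no margin, interval criterion or decision rule for concluding that a variable does not mediate.

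**The concern.** Making no prediction about worry and predicting that worry does not mediate are different claims. The first needs no evidence. The second needs evidence of absence, and a test designed to find mediation cannot supply it by failing to find it. With such a test, the noisier the data, the more likely the result is to look favourable to hypothesis 6.

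The precondition adds to this. If hypothesis 6 is true because SlowMo leaves worry unchanged, a 5% test of the effect on worry will be non-significant in about 95% of trials. The indirect effect would then usually not be estimated at all, in just the situation where an interval around it is needed.

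At stake is the specificity claim that SlowMo works through reasoning and not through worry. The Discussion expects evidence on mechanisms to inform theory and later treatment development, so an unsupported claim of specificity could carry weight.

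**Working it through.** **Inputs from the Sample size section.** 150 analysed per group, two-sided alpha 0.05, a 10-point target on the Green Paranoid Thoughts Scale (GPTS) with SD 25 (10/25 = 0.4 SD), 10 therapists in the SlowMo arm with ICC 0.01, and 360 recruited with 20% attrition (360 × 0.8 = 288).

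**Step 1: the plan's own power figure.** Power ≈ Φ(d/√(2/n) − 1.96), with √(2/150) = 0.1155.
- d = 0.4: 0.4/0.1155 = 3.464, and Φ(1.504) = 0.934. The exact t calculation gives 93.2%. With a design effect of 1 + (15 − 1) × 0.01 = 1.14 in the SlowMo arm it is 91.8%, against the stated 90%.
- d = 0.35: 85.6% by t test and 83.4% with clustering, against the stated 80%.

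The stated figures are reproduced or slightly conservative. The mediation power cannot be reproduced, because its path coefficients and residual SD are not given.

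**Step 2: the precondition applied to worry.** The same formula with 150 per arm, where d is the true standardised effect on worry (assumed):
- d = 0.2: 0.2/0.1155 = 1.732, and Φ(−0.228) ≈ 0.41. It is missed in about 59% of trials.
- d = 0.3: 0.3/0.1155 = 2.598, and Φ(0.638) ≈ 0.74. It is missed in about 26% of trials.

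This covers only the effect on worry. The precondition also needs a significant effect on paranoia, which lowers the chance of passing a little further.

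**Step 3: the whole route.** A simulation used N = 300, a total effect of 0.4 SD and 4,000 runs per scenario. It required a significant effect on worry, a significant effect on paranoia, and joint significance of the two paths. Here a is the effect of treatment on worry and b the effect of worry on paranoia; all path values are assumptions.

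| True situation | No mediation finding |
|---|---|
| a = 0 (b = 0.3 or 0.5), no mediation | about 96% |
| a = 0.2, b = 0.2 to 0.5 (10% to 25% mediated) | 60% to 65% |
| 30% mediated (a = 0.24 to 0.4) | 13% to 49% |
| 40% mediated (a = 0.32 or 0.4) | 11% to 24% |

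A non-finding therefore separates no mediation from modest mediation poorly.

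**Step 4: could absence be tested?** For illustration, take a margin of 3 GPTS points (30% of the 10-point target; 3/25 = 0.12 SD), N = 288 and a = 0, ignoring clustering. SE(a) = 2/√288 = 0.118, and SE(ab) ≈ b × 0.118. The chance that a one-sided 95% upper bound falls below the margin is Φ(0.12/SE(ab) − 1.645).
- b = 0.3: SE = 0.035, and Φ(1.75) = 0.96.
- b = 0.5: SE = 0.059, and Φ(0.39) = 0.65.

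In the simulation with a = 0, the half-width of the 95% interval for the indirect effect, as a share of the 0.4 SD total, was 0.17 (b = 0.3) to 0.28 (b = 0.5). Only a margin of roughly 0.2 to 0.3 of the total effect, or wider, is realistic at this sample size.

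**The case against.** The strongest reply is that a margin and decision rule for a secondary mechanistic hypothesis belong in the statistical analysis plan, which is not shown, and that a journal article condenses the full protocol. That stands as far as the missing margin goes. It does not cover what the article itself fixes: a hypothesis worded as a null, at odds with its own Aims, beside an analysis that works in one direction only.

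A reader might infer that the investigators will treat a non-significant or unrun test as confirmation of hypothesis 6. The article does not say so. The promise in the Aims to examine observed effects shows that the prediction is open to refutation.

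A reader might also take the precondition to cover worry explicitly. It does not. It refers to the putative mediator, and the section on assessment of efficacy names only the belief-flexibility measures and the beads task as hypothesised mediators, with worry listed elsewhere. Applying it to worry is the natural reading, because no other mediation analysis is described, but it remains a reading. As a secondary outcome, worry will in any case have its treatment effect estimated, so the first leg of the indirect effect will be available.

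Two further inferences fail. The power above 70% for 30% mediated is tied to the pilot work on reasoning and cannot simply be carried over to worry. Nor should attrition be counted again on top of it, since N = 300 is already close to the 288 expected after 20% loss.

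Finally, a narrow interval does not settle the matter alone. The article itself calls confounding of mediator and outcome the major challenge, and that applies equally to a claim of no mediation.

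**Conclusion.** The point holds in a limited form. Hypothesis 6 asserts more than the Aims do, and the analysis described offers no result that could support it: a failed precondition or a non-significant indirect effect leaves modest mediation by worry quite possible. The size is shown by the 59% and 26% chances of missing true effects on worry of 0.2 and 0.3 SD. These rest on 150 per arm, a simple two-sample test without clustering, and the reading that the precondition applies to worry. The simulated rates and the 65% to 96% feasibility range depend on assumed path values and an illustrative margin, none of which comes from the protocol.

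The severity is minor. This is a secondary hypothesis. Mediation by worry is not among the main research questions, and the primary efficacy test and the test of mediation through fast thinking are unaffected.

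**What to change.** 1. Reword hypothesis 6 to match the Aims: no mediation by worry is predicted, and the indirect effect through worry will be estimated.
2. Estimate and report that indirect effect with its confidence interval whether or not treatment effects on worry and paranoia are significant.
3. State that worry does not materially mediate only if the interval excludes a margin that the sponsor sets and justifies before the data are seen. Otherwise report the result as inconclusive. The 3-point margin above is an illustration, not a recommendation.
4. Carry the planned sensitivity analysis for hidden confounding over to the worry result, and word any conclusion accordingly.

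The cost is one or two sentences and a little extra analysis, with no new data. The downside is that hypothesis 6 may end as inconclusive: with the illustrative margin and b = 0.5, this would happen in about 35% of trials (1 − 0.65) even if SlowMo had no effect on worry.
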